# Online and Recovery-Oriented Support Groups Facilitated by Peer Support Workers in Times of COVID-19: Protocol for a Feasibility Pre-Post Study

**DOI:** 10.2196/22500

**Published:** 2020-12-18

**Keywords:** peer support workers, internet-based peer support groups, personal-civic recovery, clinical recovery, COVID-19 Stress Scales, peer support, feasibility, mental health, COVID-19, intervention, recovery

## Abstract

**Background:**

In times of pandemics, social distancing, isolation, and quarantine have precipitated depression, anxiety, and substance misuse. Scientific literature suggests that patients living with mental health problems or illnesses (MHPIs) who interact with peer support workers (PSWs) experience not only the empathy and connectedness that comes from similar life experiences but also feel hope in the possibility of recovery. So far, it is the effect of mental health teams or programs with PSWs that has been evaluated.

**Objective:**

This paper presents the protocol for a web-based intervention facilitated by PSWs. The five principal research questions are whether this intervention will have an impact in terms of (Q1) personal-civic recovery and (Q2) clinical recovery, (Q3) how these recovery potentials can be impacted by the COVID-19 pandemic, (Q4) how the lived experience of persons in recovery can be mobilized to cope with such a situation, and (Q5) how sex and gender considerations can be taken into account for the pairing of PSWs with service users beyond considerations based solely on psychiatric diagnoses or specific MHPIs. This will help us assess the impact of PSWs in this setting.

**Methods:**

PSWs will lead a typical informal peer support group within the larger context of online peer support groups, focusing on personal-civic recovery. They will be scripted with a fixed, predetermined duration (a series of 10 weekly 90-minute online workshops). There will be 2 experimental subgroups—patients diagnosed with (1) psychotic disorders (n=10) and (2) anxiety or mood disorders (n=10)—compared to a control group (n=10). Random assignment to the intervention and control arms will be conducted using a 2:1 ratio. Several instruments will be used to assess clinical recovery (eg, the Recovery Assessment Scale, the Citizenship Measure questionnaire). The COVID-19 Stress Scales will be used to assess effects in terms of clinical recovery and stress- or anxiety-related responses to COVID-19. Changes will be compared between groups from baseline to endpoint in the intervention and control groups using the Student paired sample t test.

**Results:**

This pilot study was funded in March 2020. The protocol was approved on June 16, 2020, by the Research Ethics Committees of the Montreal Mental Health University Institute. Recruitment took place during the months of July and August, and results are expected in December 2020.

**Conclusions:**

Study results will provide reliable evidence on the effectiveness of a web-based intervention provided by PSWs. The investigators, alongside key decision makers and patient partners, will ensure knowledge translation throughout, and our massive open online course (MOOC), *The Fundamentals of Recovery*, will be updated with the evidence and new knowledge generated by this feasibility study.

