#### Principal Research Questions

The principal research questions are whether our novel PSWs-facilitated online intervention will have an impact in terms of (Q1) clinical recovery potential and (Q2) personal-civic recovery potential. We also question (Q3) how these potentials can be impacted by the COVID-19 pandemic and (Q4) how the lived experience of people in recovery can be mobilized to cope with the situation. Finally, we also explore (Q5) how sex and gender considerations can be taken into account for the pairing of PSWs with service users beyond considerations based solely on psychiatric diagnoses or specific MHPIs [35]. We aim to collect data for a future randomized controlled trial (RCT) [36] by clarifying a certain number of remaining uncertainties and by detecting an effect that would be specifically attributable to transitional peer support as facilitated by trained PSWs. We will thus consider scientific reasons, processes, resources, and management in preparation for a more definitive trial. Indicators of feasibility will include recruitment rates practices, participants and facilitators, as well as feasibility and retention rates in the study protocol [37].

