
#### How Results Will Be Used

A result of PSWs’ online group intervention efficacy in terms of both clinical and personal-civic recovery potentials for people living with psychotic disorders, and/or anxiety and mood disorders, would privilege the role of PSWs in recovery-oriented peer-to-peer support groups. The study will impact the conceptualization of recovery- and citizenship-oriented mental health care, clinical training, and in mental health treatment resource allocation and for informing nonspecialized clinicians as well as the public. Indeed, an embedded observational and qualitative study performed with postgraduate students and patient research partners will improve the understanding of the experiential knowledge translation and knowledge sharing dynamics among participating patients living with MHPIs and among PSWs. Decision making will also be informed for the definition of a university mission for all psychiatric facilities of the University of Montreal’s Integrated University Health and Social Services Network (IUHSSC). This network advances the integration of the university mission of care, teaching, and research, by facilitating knowledge translation and technology assessment in order to improve access to evidence-based care. This is a vast integrated network of health and social services organizations and public establishments with a university vocation, including those psychiatric facilities where PSWs do their final internship before being eventually hired. The territory of this network represents 46% of the population of the province of Quebec and the three Integrated University Health and Social Services Centers affiliated with the University of Montreal are partners of this study. Since 2015, the IUHSSC organization is the gateway to the public service system where the Quebec population can turn in case of health problems and/or psychosocial problems, including MHPIs. Due to their university affiliation, their mission is to contribute to academic training as well as to the development and dissemination of scientific knowledge. The study will inform the PSWs’ training program by generating a better understanding of the specific effects attributable to the PSW group intervention.

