#### Allocation

Upon reception of the signed Information and Consent forms by email, consecutive referrals will be randomly allocated by computer algorithm to one of the two modalities at point of entry into the study on acceptation into the protocol using a computerized program (eg, randomization.com). At this entry point, the participant will have been evaluated, diagnosed, met inclusion criteria, and given formal consent for the randomization procedure. To ensure a balance in the allocation for the strata and thus control the risk of a secular trend in the composition of groups, random block sizes in a random order will be used (3, 6, 9, etc). Participants will thus be randomly allocated to the trial arm (n=20, 2 groups of 10) or control arm (n=10), and will be identified by a randomly assigned identification number. Among those allocated to the experimental groups, 10 patients with psychotic disorders will be randomly selected to be part of the transitional support group for patients with psychotic disorders, and 10 patients with anxiety or mood disorders will be randomly selected to be part of the transitional self-help group for patients with anxiety or mood disorders. It will be the same for the control group; 5 patients with psychotic disorders will be randomly selected to be part of the control group for patients with psychotic disorders, and 5 patients with anxiety or mood disorders will be randomly selected to be part of the control group for patients with anxiety or mood disorders. In both cases, those who have not been selected will be placed on a substitute list in the event of withdrawal of a selected patient, who will be replaced at random by one of the corresponding substitutes.

The groups will be studied together and separately: the experimental group for patients with psychotic disorders (n=10) will be compared to the control group for patients with psychotic disorders (n=5); the experimental group for patients with anxiety or mood disorders (n=10) will be compared to the control group for patients with anxiety or mood disorders (n=5); and the combined experimental group for patients with psychotic disorders and for patients with anxiety or mood disorders (n=20; 2×10) will be compared to the combined control group for patients with psychotic disorders and anxiety or mood disorders (n=10).

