#### Primary and Secondary Outcome Measures

Several instruments have been developed by clinicians and academics to assess clinical recovery. Based on their life narratives and to assess personal-civic recovery, measurement tools have also been developed through community-based participatory research and validated by persons living with MHPIs (eg, the Recovery Assessment Scale and the Citizenship Measure questionnaires). As users of mental health services typically tend to prefer interventions to help them recover, reintegrate with society, and achieve their personal goals [92], we propose this pre-post research feasibility trial design to evaluate the outcomes on personal-civic recovery (primary outcome), on clinical recovery and stress- or anxiety-related responses to the COVID-19 pandemic (secondary outcome).

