**Figure 2 figure2:**
[figure not shown]
Weekly variations in new registrants to the MOOC (massive open online course) during the first 20 weeks of 2020. WHO: World Health Organization.

In 2017, before the current COVID-19 crisis, Bendezu-Quispe and colleagues [114] suggested that the emergence and re-emergence of communicable infectious diseases like Ebola or Zika were already increasing the necessity of knowledgeable and skilled health professionals, specifically with MOOCs arising as opportunities that allow people around the world to participate in higher-education courses. They argued that MOOCs can be used to learn about health issues of global relevance, and with the necessity of fast divulgation of knowledge and skills. Given the scope of mental health problems and the constraints of resources in training psychiatrists and other mental health professionals in most parts of the world, continuing education for medical and health or social services professionals and students, including in primary care, is vital [115]. In this MOOC, PSWs are included as training partners, as well as a subgroup of colearners.

Moreover, millions of people worldwide experienced moderate to severe levels of stress- or anxiety-related symptoms in response to COVID-19. This is true for the general population [116] as well as for people already diagnosed with psychotic disorders [117] or anxiety and mood disorders [118]. Yet, if general conditions remain the same for the participants of the experimental groups and for those of the control groups, and significantly different benefits are still observed among these groups, these differences will, in principle, be attributable to the intervention and not to the pandemic context.

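### The article promises reliable effectiveness evidence and a PSW-specific effect; a 20 versus 10 comparison with usual care supports neither claim

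*Protocol article*

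**What the plan says.** The Abstract's Conclusions are unhedged: "Study results will provide reliable evidence on the effectiveness of a web-based intervention provided by PSWs". In the Introduction, the Principal Research Questions section pairs the collection of data for a later randomised trial with a second aim: "detecting an effect that would be specifically attributable to transitional peer support as facilitated by trained PSWs". The section How Results Will Be Used repeats this, expecting a better understanding of the "specific effects attributable to the PSW group intervention".

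The design behind these statements is as follows.

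- The Abstract's Methods say: "Random assignment to the intervention and control arms will be conducted using a 2:1 ratio". The Allocation section fixes 20 experimental and 10 control participants.
- That section adds: "The groups will be studied together and separately". This gives two 10 versus 5 comparisons by diagnosis and one combined 20 versus 10 comparison.
- Under Control Intervention, controls get usual outpatient care, and experimental participants get the same care plus the PSW-led online group.
- Primary and Secondary Outcome Measures makes personal-civic recovery primary. It is measured by two questionnaires, and no single primary quantity is named.
- Quantitative Analyzes names a paired t test with the arms run separately, and a comparison of confidence intervals and effect sizes between groups.
- No significance level, power, target difference or sample-size rationale is given.

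**The concern.** There are two claims, and each needs something the design lacks.

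**Reliable evidence of effectiveness** needs a between-arm estimate precise enough to separate a useful effect from none. Thirty participants look far too few for that.

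**An effect specific to PSW facilitation** needs a comparison in which that component differs and the rest of the package does not. Here everything added to usual care differs between the arms.

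The stakes are practical. How Results Will Be Used says a favourable result would strengthen the role of PSWs and bear on resource allocation and training. The Discussion raises wider access across three centres with more than 40,000 employees. Overstated claims would feed into those decisions.

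**Working it through.** The article contains no sample-size calculation, so there is no figure to reproduce.

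**Inputs**
- Arm sizes 20 and 10, and 10 and 5 within each diagnosis (Allocation).
- Completed at follow-up (T2, Table 1): 7 + 10 = 17 experimental and 7 control, so 24 of 30 (80%).
- SDs 0.78 (Recovery Assessment Scale) and 0.63 (Citizenship Measure), from the earlier validation study (Recruitment).
- Assumed, because not stated: two-sided 0.05, 80% power, baseline/follow-up correlation ρ from 0.5 to 0.8, independent participants.

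**Power and precision**

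The two-sample t statistic has df = n₁ + n₂ − 2 and non-centrality d / √(1/n₁ + 1/n₂). The 95% half-width in SD units is t(0.975, df) × √(1/n₁ + 1/n₂). For 20 versus 10, √(1/20 + 1/10) = 0.387 and t = 2.048, so the half-width is 0.793.

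| Comparison | Detectable d, 80% power | Power at d = 0.5 | Power at d = 0.8 | 95% CI half-width |
|---|---|---|---|---|
| 20 vs 10 | 1.12 | 24% | 51% | ±0.79 SD |
| 17 vs 7 | 1.32 | 19% | 40% | ±0.93 SD |
| 10 vs 5 | 1.66 | 13.5% | 27% | ±1.18 SD |

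Here d is in SDs of the score analysed.

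**In scale points, 20 versus 10**

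The SD of a change score is SD × √(2(1 − ρ)).
- Recovery Assessment Scale, ρ = 0.5: 1.124 × 0.78 × 1.000 = 0.88 points.
- Recovery Assessment Scale, ρ = 0.8: 1.124 × 0.78 × 0.632 = 0.55 points.
- Citizenship Measure: 1.124 × 0.63 = 0.71 points at ρ = 0.5, and 0.71 × 0.632 = 0.45 at ρ = 0.8.

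Baseline adjustment multiplies the raw SD by √(1 − ρ²). The detectable difference becomes 1.124 × 0.866 = 0.97 raw SD at ρ = 0.5 and 1.124 × 0.600 = 0.67 at ρ = 0.8. In that best case a raw difference of 0.5 SD is 0.5 / 0.6 = 0.83 residual SD, so power is only slightly above the 51% shown for 0.8.

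**What 80% power would need**

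At 2:1, by the normal approximation, the control arm needs 1.5 × (1.960 + 0.842)² / d².
- d = 0.5: 47.1, so 48 controls and 144 in total; 144 / 0.8 = 180 with 20% loss.
- d = 0.8: 18.4, so 19 controls and 57 in total; 57 / 0.8 = 71.3, so 72 with 20% loss.

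**Attribution**

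Experimental arm minus control arm = (usual care + PSW facilitation + group contact + recovery content + online format) − (usual care). Group contact is 10 × 90 minutes = 15 hours. The components always occur together, so only their sum can be estimated. This needs no numerical assumption.

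**The case against.** The strongest reply is that the document calls itself a feasibility study, places itself before a future randomised trial and names recruitment and retention as indicators. A small sample is then no fault. That stands, and it is why the point concerns the claims and not the size. The attribution phrases can also be read as meaning the whole PSW-led package. That reading is possible, but the word *specifically* and the use of the results for PSW training point to the narrower one. A high baseline correlation helps; the range above allows for it, and the conclusion survives.

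A reader might infer more than the documents support:

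- *The Discussion attributes differences to PSWs.* It says "these differences will, in principle, be attributable to the intervention and not to the pandemic context". That separates the intervention from the pandemic, is conditional and hedged, and claims nothing about the PSW component.
- *The design repeats the gap it set out to close.* The section on why a feasibility study is needed describes a different gap: earlier effects might be due to other professionals in teams with PSWs. Adding a PSW group to usual care, with PSWs kept apart from clinic therapists, does address that.
- *Many outcomes are tested without adjustment.* The article is silent on significance level and adjustment, and an analysis plan not shown may settle both.
- *The detectable difference nearly exhausts the room left on the scale.* The intervention also aims to prevent deterioration, so a difference can arise from decline in controls. The quoted means also predate the trial.

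**Conclusion.** The concern holds as a mismatch between claims and design. Under two-sided 0.05 and 80% power, the full sample can reliably detect only a difference of about 1.1 SD of the change score, or 0.67 to 0.97 raw SD with baseline adjustment. Follow-up losses and the diagnostic split make this worse. Any correlation among members of the same workshop group would reduce precision further. An effect of moderate size would most likely be missed, and any estimate will carry a wide interval.

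The PSW-specific claim fails for a structural reason that a larger sample would not cure. Randomisation can support a statement about adding the package to usual care, but not about which part of it worked. The study's value as preparation for a larger trial is not in question.

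**What to change.** 1. In the Abstract's Conclusions, replace the effectiveness sentence with: *will provide feasibility data and preliminary estimates of effect*.
2. In Principal Research Questions and How Results Will Be Used, replace the PSW-specific attribution with: *the effect of adding a PSW-led online group to usual care*.
3. Keep personal-civic recovery as the primary outcome and name one quantity: the mean of its 47 items (24 Recovery Assessment Scale plus 23 Citizenship Measure) in the combined 20 versus 10 comparison. Report it as a baseline-adjusted between-arm difference with a 95% confidence interval.
4. Label the within-diagnosis comparisons and all other scales exploratory.
5. Report recruitment and retention with 95% confidence intervals as the feasibility indicators already named. Do not make them primary now: personal-civic recovery is fixed as primary, and Table 1 already reports follow-up completion.

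Because follow-up questionnaires are already in, item 3 should be dated, with a statement of whether any between-arm result had been seen. No change to sample, control or data collection is needed. The cost is a less favourable stated claim.

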**Trial Registration:**

ClinicalTrials.gov NCT04445324; https://clinicaltrials.gov/ct2/show/NCT04445324

**International Registered Report Identifier (IRRID):**

PRR1-10.2196/22500

## Introduction

### Need for a Feasibility Trial

In recent pandemics, social distancing, isolation, and quarantine have precipitated depression and anxiety [1,2]. It is expected that isolation and physical (social) distancing due to the COVID-19 pandemic will lead to similar consequences as confined people are detached from their loved ones, deprived of personal liberties, and devoid of purpose owing to altered routine and livelihood. These consequences will probably be amplified by the economic recession and the ensuing increase in unemployment and poverty. Moreover, those with pre-existing mental illness might suffer from limiting interpersonal interactions that are central to their management, as well as reduced access to helpful but “nonessential” (and thus often canceled) psychiatric services [3]. Successful use of quarantine and distancing as a public health measure requires us to reduce, as much as possible, the negative effects associated with it [4].

In response to this situation, this feasibility study of a trial offers a transitional measure of online social support for people suffering from (1) psychotic disorders or (2) anxiety or mood disorders, and to assess its effects in terms of both personal-civic recovery and clinical recovery. Transitional peer support groups will be organized and led by trained peer support workers (PSWs). PSWs are persons with first-hand lived experience of mental health problems or illnesses and who are further along in their own recovery journey. Upon training, they can provide supportive services when hired to fill such a paid specialty position, as now recommended by recovery-oriented best practices guidelines [5,6]. Indeed, recovery focuses on how individuals can have more active control over their lives (agency) [7]. It is characterized by a search for the person’s strengths and capacities, satisfying and meaningful social roles, and mobilizing formal and informal support systems. Peer support has thus become one predominant feature of the recovery paradigm and, as per their title and function, PSWs specialize in peer support.

#### A Problem to Be Addressed: Measuring the Effects of PSWs on Recovery

In Canada, the incremental economic burden of mental health problems or illnesses (MHPIs), which incorporates the use of medical resources and productivity losses due to long-term and short-term disability, as well as reductions in health-related quality of life, is estimated to be more than $50 billion per year. By calculating all health services utilization, long-term and short-term work loss, and health-related quality of life and their dollar valuations, Lim et al [8] have concluded that over one-half was due to reductions in health-related quality of life. Decreasing pain and suffering, overcoming disability due to MHPIs, and helping Canadians affected by MHPIs to recover, instead of solely treating them for their MHPIs, is a major public health issue, even more so in times of isolation and quarantine in the midst of a pandemic since social support is known to be an important factor that can affect mental health [9]. This is why, along with other sociopolitical or historical considerations, recovery is now the official leading paradigm in the transformation of mental health systems and policies in Canada [10], as is also the case in the United States [11], the United Kingdom [12], and elsewhere in the world, and as promoted by the World Health Organization (WHO) [13].

As a social movement echoing the historical claims of other social movements since the 1960s and 1970s, including the antipsychiatry movement, the origins of recovery in mental health are now fairly well documented [14,15]. Yet, tensions persist about the meaning and ownership of recovery [16,17]. Generally speaking, there are two major portrayals of recovery [18,19]. One is akin to the notion of cure in the field of physical health; *clinical* recovery refers primarily to the reduction of psychiatric symptoms through a curative approach to the disease using psychopharmacology and psychotherapy. With this first axiom of recovery, the role of the ill person is mainly to follow the instructions of professionals and comply with prescribed treatments. On the other hand, a more *personal-civic* axiom of recovery promotes the empowerment of the persons, their ownership and authorship of their own history, their autonomy, and their independence in living free from any labeling diagnosis [20]. Recovery is not the disappearance or the eradication of symptoms but a redefinition of oneself in light of lived experience as a person who managed to live with an MHPI, and who found a new balance in life toward well-being and quality of life, with or without enduring psychiatric symptoms or treatment.

The experience of living in recovery is particularly useful for sharing among peers who are coping, and/or have coped, with similar issues. The commonality is the struggle and emotional pain that can accompany the feeling of loss and/or hopelessness due to the consequences of MHPIs, rather than in relation to a specific symptom or psychiatric diagnosis. This commonality might also be in relation to sex and gender considerations [21,22], more than in relation to specific conditions. Peer-to-peer communication is a widespread phenomenon (eg, in groups like Alcoholics Anonymous [23] or Al-Anon for families [24]). Access to PSWs has been widely advocated internationally by service user researchers [25,26] and by professional organizations [27,28]. Provision of peer support has been identified as a fidelity requirement for recovery-orientated services [11,29] where the PSWs bring a focus on health, recovery, and quality of life, rather than on illness and disability [30]. They provide the mental health service users a validation of their lived experience and unique experiential knowledge for facilitating the reclaiming of their lives as full members of the community and for remaining so [31]. The Mental Health Commission of Canada emphasizes that patients living with MHPIs who interact with PSWs “will not only feel the empathy and connectedness that comes from similar life experiences, but that this interaction also fosters hope in the possibility of a recovery that includes health, wellbeing, quality of life, and resilience” [32]. Since 2005, recovery and PSWs have also been at the core of Mental Health Action Plans in the province of Quebec [33,34]. Yet, we still do not know how a recovery-oriented mental health organization that would include PSWs as staff members would improve recovery from the perspective of persons living with MHPIs.

